## ***Randomization and blinding***

Randomization will be conducted as participants are enrolled, using block randomization with a computer-generated random sequence (blocks of size four). A designated data manager, who is not involved in recruitment, intervention, or evaluation, will generate and securely store the random sequences in IBM SPSS, version 26.0.1. To conceal group allocation, an independent researcher not involved in the trial will place assignment codes into sequentially numbered, sealed, opaque envelopes according to the computer-generated random sequence. When each envelope is opened, participants will be assigned to either the control group or the trial group based on the corresponding “0” or “1” on the random number card. At enrollment, a physician not involved in randomization will assess potential participants, and the assignment group will be revealed onsite by opening the sealed envelopes, ensuring a 1:1 randomization ratio. Permuted blocks of size four will be used to maintain balanced allocation. Blinding physicians and volunteers to group assignments is not feasible, and participants are similarly unblinded due to self-reported outcomes. Assessors are also not blinded; however, to minimize bias, the trial hypothesis is not disclosed to either assessors or participants. The randomization list will remain secured (both physically and digitally), accessible only to the primary investigator and the designated data manager, thus maintaining its integrity throughout the study.

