## **Study design**

This is a randomized controlled trial with two parallel arms, conducted in an open-label, difference-test manner, following a 1:1 allocation ratio, within a single-center over a span of 8 weeks. The trial follows the recommendations of the Standard Protocol Items: Recommendations for Interventional Trials (SPIRIT) statement. A completed SPIRIT checklist can be found in online supplemental material I. This study has received approval from the Ethics Committee of West China Hospital, Sichuan University. Any significant protocol modifications will be submitted to the Biomedical Ethics Committee of West China Hospital, Sichuan University for review. The study protocol has been registered at the Chinese Clinical Trial Registry (ChiCTR2300071560). The current study protocol is the sixth version updated on April 21, 2025.

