## **Setting & Recruitment**

Participants will be recruited from the Specialist Outpatient Clinic at West China Hospital, Sichuan University. Individuals who meet the eligibility criteria will be informed about the trial procedures and enrolled upon providing written informed consent; those who do not meet the criteria will receive standard treatment in accordance with the trial protocol. To ensure an

adequate sample size, standardized training and supervision will be provided to researchers, improving the success rate of informed consent acquisition. The trial aims to recruit 78 participants, and additional strategies (e.g., referrals from medical examination centers or relevant departments, poster campaigns) will be employed to facilitate timely enrollment. Recruitment will commence within one year of the scheduled enrollment date and will proceed based on site readiness. Details on data collection and intervention administration are available in Supplemental Material II. All eligible participants who agree to partake in the trial will be randomly assigned and briefed on the required procedures and written informed consent (accessible in Supplemental Material III) must be provided prior to enrollment. Baseline data for both groups will be gathered via a questionnaire administered before the intervention in Room 902 of the Special Needs Outpatient Department, collecting demographic information (e.g., gender, age, height, weight, occupation, education), potential causes of back pain, physical activity level, medical and exercise treatment history, duration of low back pain, severity of low back pain (current, worst, and least), level of functional impairment, and types of pain avoidance behaviors (see Supplemental Material II). Experienced physical therapists, who are independent of the trial design, intervention, and statistical analysis, will perform outcome measurements at baseline, after the 4-week intervention, and after the 8-week intervention, as illustrated in Figure 1.

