### **App-based exercise therapy**

During the initial visit, the physician implements app-based exercise therapy in three parts: (1) guiding the patient through the “ShuKang PRO” app login, (2) formulating an individualized exercise prescription, and (3) demonstrating the exercises and providing instructions to the therapist (Figure 2). Table 2 outlines the specific exercises taught by the therapist responsible for the intervention. Exercise prescriptions are derived from baseline data and FITT-VP principles, primarily emphasizing core stability and motor control training recommended by clinical guidelines. The physician adjusts the stepwise treatment plan according to individual variability.

To improve compliance with wearing the wearable device at home, a fabric fixture has been developed to hold the device nodes securely and ensure correct positioning. The wearable device uses noninvasive Inertial Measurement Units (IMUs) to capture body acceleration, angular velocity, and orientation without direct skin contact. Prior to public release, we will seek regulatory medical device approval to ensure convenience and comfort for daily use. By tracking motion

features, the device recognizes whether the prescribed movements have been completed. Before each session, patients can review the number of exercises, estimated duration, exercise preview, and written instructions. Upon reaching the upper or lower limit of the prescribed duration, the system alerts patients to begin a finishing stretch or end the exercise. Patients are then encouraged to aim for the targeted standard and are asked to fill in the Rating of Perceived Exertion (RPE) scale, which serves solely as feedback on exercise intensity and is not used as an outcome measure. The physician modifies the prescription based on the principles of overload and gradual progression in exercise volume, by adjusting the duration or repetition of each exercise.

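### Fixed blocks of four, written into the protocol of an open-label single-centre trial, leave about 25 of 78 allocations deducible in advance, and the primary investigator's list access is not tied to exclusion from recruitment

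*Protocol*

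**What the plan says.** The Protocol, under Randomization and blinding, gives the block size twice: allocation is done "using block randomization with a computer-generated random sequence (blocks of size four"), and later "Permuted blocks of size four will be used to maintain balanced allocation". No other size and no variation in size is mentioned.

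Under Study design the trial is "conducted in an open-label, difference-test manner", "following a 1:1 allocation ratio, within a single-center over a span of 8 weeks". No stratification factor is named, so there is one running sequence. Under Setting & Recruitment, "The trial aims to recruit 78 participants".

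On concealment, a data manager with no role in recruitment, treatment or assessment generates the sequence. An independent researcher fills numbered, opaque, sealed envelopes, which are opened on site. The physician who assesses candidates at enrolment is said to have no part in the randomisation. The same section also says "Blinding physicians and volunteers to group assignments is not feasible". Under App-based exercise therapy, "During the initial visit, the physician implements app-based exercise therapy in three parts", so a physician learns who is in the trial group.

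The list is "accessible only to the primary investigator and the designated data manager". No statement keeps the primary investigator out of recruitment or eligibility assessment.

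**The concern.** Concealment has two parts: nobody can read the next assignment, and nobody can work it out. The envelopes deal with the first. Fixed blocks of a known size weaken the second, because each block must close with two patients per arm. In one clinic with one sequence and visible arms, the earlier allocations are available to anyone who keeps count.

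Foreknowledge matters where staff can influence who enters, or when. Some eligibility criteria in Table 1 need judgement, such as pain due to other disease, the severity of cardiovascular disease, or the ability to use a smartphone. The timing of enrolment is also in the clinic's hands. Both primary outcomes (NRS and RMDQ) are self-reported by participants who know their arm, so any selection by expected arm would add to reporting bias.

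List access is a separate exposure. A person who holds the list needs no deduction and foresees all allocations, not a share of them.

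**Working it through.** **Inputs from the Protocol.** Block size 4 (Randomization and blinding); ratio 1:1, hence two patients per arm in each block (Study design); one sequence, as no stratification is named; N = 78 (Setting & Recruitment; Sample size).

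**The plan's own figure.** The Protocol gives no predictability figure. The one stated number used here is the total N: 58 / (1 − 0.25) = 77.3, rounded up to 78. This is reproduced.

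**Certain allocations in a block of four.** There are 6 equally likely orders. An allocation is certain once one arm has used both its places.
- 1st and 2nd: never certain.
- 3rd: certain if the first two went to the same arm, which happens in 2 of 6 orders, probability 1/3.
- 4th: always certain.

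Expected number per block = 1/3 + 1 = 4/3, and (4/3)/4 = 33.3%.

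**Applied to 78.** 78 = 19 × 4 + 2. The last two patients open an incomplete block and contribute none. 19 × 4/3 = 25.3, and 25.3/78 = 32.5%.

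**Best-guess accuracy.** The observer guesses the arm with more places left, or tosses a coin on a tie. By position, the chance of being right is 1/2, 2/3, 2/3 and 1. The third value is 1/3 × 1 + 2/3 × 1/2. The sum is 2.833, and 2.833/4 = 70.8% per full block. Over 78: (19 × 2.833 + 1/2 + 2/3)/78 = 55.0/78 = 70.5%.

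**Varying block sizes.** These come from a simulation of 3,000 sequences of 78. Sizes are drawn with equal probability (an assumption), and the observer knows the set of sizes but not their order.

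| Block sizes | Certain allocations | Best-guess accuracy |
|---|---|---|
| 4 (as written) | 32.5% | 70.5% |
| 2, 4, 6 | 4.2% | 70.1% |
| 4, 6 | 5.5% | 69.1% |
| 4, 6, 8 | 2.3% | 67.8% |

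Varying the size removes most of the certainty and little of the guessing advantage. Including blocks of 2 gives back nearly all of the small gain in guessing, because they are the most predictable: 75% best-guess accuracy taken alone.

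**List access.** For a list holder the foreseeable share is 78/78. Whether this matters depends on that person's role, which the Protocol does not state.

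**The case against.** Fixed blocks of four are a common choice, and the Protocol has real safeguards: an independent data manager, an independent preparer of envelopes, and an assessing physician with no part in the randomisation. Data management and auditing adds visits twice a month and checks of a random 20% of participants, covering eligibility and consent. These stand, and they make steering harder. They do not stop deduction, which needs only the block size and a count of past arms.

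Four stronger readings are tempting and are not supported.

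- A reader might infer that staff do foresee a third of allocations. That needs one person who knows the block size, tracks every earlier arm and can affect enrolment. The Protocol speaks of physicians and researchers in several roles and never says that they are the same individuals. Nor is the block size shown to be widely known: it is written in the protocol staff work from, and Data sharing plans no public access to the full protocol. Foreknowledge is feasible, not established.
- A reader might infer that list access in itself breaks concealment. It does so only if the primary investigator recruits or assesses eligibility, which is neither stated nor excluded.
- A reader might set 70.5% best-guess accuracy against 50% and blame fixed blocks for the whole gap. The 50% belongs to simple randomisation. Any small-block scheme, including the one proposed below, stays well above it.
- A reader might infer that resulting bias could never be corrected. NRS and RMDQ are measured at baseline, so selection on measured severity could be seen and partly adjusted for. Selection on unmeasured traits such as motivation could not.

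**Conclusion.** The point holds as a weakness in the design that is cheap to remove. It is not an internal contradiction or an arithmetic error, and it is not evidence that allocation has been or will be subverted. As written, about 25 of 78 allocations (32.5%) are certain in advance for a person who knows the block size and tracks earlier arms. This rests on one unstratified sequence run through to 78. The list access is a distinct gap: the Protocol bars the data manager from recruitment and makes no such statement about the primary investigator. The exposure is every allocation if that person recruits or assesses eligibility, and none by this route otherwise.

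**What to change.** Generate the list, or its unused part, with randomly varying block sizes such as 4, 6 and 8, and avoid blocks of 2. Keep the sizes from recruiting staff and out of the protocol they work from; the protocol text need say only that permuted blocks of varying size are used. Restrict list access to the data manager until enrolment is complete or the database is locked. The trial is open-label, so nobody needs the list to learn a treated patient's arm.

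The cost is a new sequence, replacement of unopened envelopes and an amendment to the randomisation text. The statistical downside is a possible final imbalance of a few participants. A last block cut short can leave a difference of up to half its size: 4 with a block of eight, against 2 with a block of four. The change should be justified by the drop in certain allocations (32.5% to about 2%, or about 5.5% with sizes 4 and 6), not by the small drop in guessing accuracy.

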## ***Interventions***

The physiotherapists who delivered the intervention in both two groups will not be involved in the outcome measures and are not blind to the group assignment. The two groups will conduct an 8-week intervention, for a total of 24 sessions. The interventions in both groups will be completed over 8 weeks, following the 2020 clinical practice guidelines of the North American Spine Association. Subjects will be encouraged to participate in the intervention and assessment throughout the trial protocol. Frequency of attendance, medication changes, adverse events, etc. will be reported by the participants to the physiotherapist in charge of the trial management and will be duly recorded in the case report form.

All participants will use the same version of the app throughout the trial. If a participant's condition worsens during treatment, they may seek other treatments (e.g., pharmacotherapy, physical therapy), but additional exercise therapy is prohibited. Participants must accurately report any extra treatments to the investigator, who will document them in the case report forms. To enhance adherence to intervention protocols, a weekly group WeChat video session will be held. This group-based health coaching allows participants to exchange peer support and psychological encouragement, thereby strengthening engagement between therapists and patients.

## **TG Therapy**

For the trial group, the intervention consisted of app-based exercise therapy (40-minute sessions, three times per week for eight weeks), patient education (10-minute sessions, once weekly for eight weeks), and WeChat video-based health coaching (20-minute sessions, once weekly for eight weeks).

### **App-based exercise therapy**

During the initial visit, the physician implements app-based exercise therapy in three parts: (1) guiding the patient through the “ShuKang PRO” app login, (2) formulating an individualized exercise prescription, and (3) demonstrating the exercises and providing instructions to the therapist (Figure 2). Table 2 outlines the specific exercises taught by the therapist responsible for the intervention. Exercise prescriptions are derived from baseline data and FITT-VP principles, primarily emphasizing core stability and motor control training recommended by clinical guidelines. The physician adjusts the stepwise treatment plan according to individual variability.

To improve compliance with wearing the wearable device at home, a fabric fixture has been developed to hold the device nodes securely and ensure correct positioning. The wearable device uses noninvasive Inertial Measurement Units (IMUs) to capture body acceleration, angular velocity, and orientation without direct skin contact. Prior to public release, we will seek regulatory medical device approval to ensure convenience and comfort for daily use. By tracking motion

features, the device recognizes whether the prescribed movements have been completed. Before each session, patients can review the number of exercises, estimated duration, exercise preview, and written instructions. Upon reaching the upper or lower limit of the prescribed duration, the system alerts patients to begin a finishing stretch or end the exercise. Patients are then encouraged to aim for the targeted standard and are asked to fill in the Rating of Perceived Exertion (RPE) scale, which serves solely as feedback on exercise intensity and is not used as an outcome measure. The physician modifies the prescription based on the principles of overload and gradual progression in exercise volume, by adjusting the duration or repetition of each exercise.

Patients can schedule exercise times using the app's alarm function. Physicians may set phased goals in advance and send weekly reminders via the app to track goal completion. After being trained in all movements at the first consultation, participants enter an eight-week program comprising three weekly sessions of 40–60 minutes under a physical therapist's supervision. Each session consists of a warm-up, functional training, and relaxation. Table 2 details the primary exercises performed during the eight weeks, and the physician tailors intensity and difficulty according to each patient's characteristics.

#### App-based patient education

During the baseline assessment, a physical therapist presents an animated educational video on chronic low back pain (CLBP). Once weekly, patients receive an illustrated educational piece about CLBP via the app, taking approximately five to ten minutes to read. Topics include the definition, pathogenesis, etiology, and diagnosis of CLBP; management of daily activities; prevention of progression and recurrence; diet and weight control. Every Friday, patients complete a self-administered CLBP knowledge questionnaire in the app to verify comprehension, rather than for statistical analysis. Patients may retake the questionnaire until they select the correct responses.

#### WeChat video-based health coaching

A weekly group WeChat video session (40 minutes) is scheduled, such that eight of the 24 sessions are therapist supervised. During these sessions, the therapist reviews each patient's

condition, diet, and weight, and patients can share experiences and support each other. This group-based health coaching fosters peer support strengthens therapist-patient rapport and builds mutual trust. The weekly meeting also allows the therapist to confirm exercise accuracy, preventing new injuries. When a patient demonstrates correct movement execution and meets progress criteria, the therapist can adjust the treatment plan accordingly.

## **CG Therapy**

The control group's interventions included paper-based exercise therapy and app-based patient education. At the initial diagnosis, physical therapists responsible solely for the intervention will provide patients with a printed exercise manual containing the same training exercises and frequency as the trial group, demonstrated once by the therapists. No further instruction will be offered during the subsequent eight weeks unless requested by the patient. The manual employs text and graphics to highlight essential elements, standards, and precautions for each movement. If patients encounter difficulties exercising at home, they may seek assistance at a designated partner community hospital or the main hospital, where physical therapists have received prior training. Over eight weeks, participants will complete 24 unsupervised self-training sessions (three times per week). In parallel, the control group will receive the same patient education content through an app that provides information once weekly for eight consecutive weeks. The app is configured only for patient education and does not grant access to the exercise training module.

## ***Outcome measures***

The outcome measures are divided into primary, secondary outcomes and other outcomes, which include pain intensity, physical function, quality of life, psychopathological symptoms, exercise compliance, fear-avoidance in exercise and catastrophizing, and adverse events. Table 3 provides an overview of the questionnaire items and the time points for outcome measurements. Changes in outcome measures will be primarily evaluated after 8 weeks of treatment.

## Primary outcomes

CLBP severity will be measured using the Numerical Rating Scale (NRS), which ranges from 0 (no pain) to 10 (severe pain). Patients select a single number (0–10) that best represents their current level of pain. The NRS is widely used due to its simplicity, ease of administration, and reliable detection of pain severity.

The Roland Morris Disability Questionnaire (RMDQ) evaluates functional status in patients with low back pain. It consists of 24 items specifically related to limitations caused by low back pain. Each item is scored as 1 (yes) or 0 (no), yielding a total score between 0 and 24, where higher scores indicate greater functional impairment.

## Secondary outcomes

The “Timed Up & Go” (TUG) test offers a rapid assessment of walking function. Patients start seated with their backs against a chair, then stand up, walk three meters, turn around, return to the chair, and sit down. The time taken (in seconds) to complete this sequence is recorded. Lower times reflect better mobility, whereas higher times indicate mobility impairment and an increased risk of falling.

The 12-item Short Form Health Survey (SF-12) measures eight dimensions of health-related quality of life. These dimensions are summarized into two component scores: the Physical Component Summary (PCS) and the Mental Component Summary (MCS). The SF-12 is shorter and easier to administer than the original SF-36, while retaining good reliability and validity.

The Depression-Anxiety-Stress Scale (DASS21) evaluates mental health based on depression, anxiety, and stress factors. It employs a 4-point Likert scale (0–3) to indicate how frequently participants experience negative emotional states. Higher scores signify more severe psychopathological symptoms.

The Exercise Adherence Rating Scale (EARS) assesses adherence to exercise programs prescribed for individuals with chronic pain. It contains 16 items grouped into three subscales that capture self-reported adherence and the reasons for compliance or non-

compliance. Wearable devices will also be used to calculate completion rates of exercise prescriptions among patients with CLBP.

